# Individualised behaviour change strategies for physical activity in multiple sclerosis (IPAC-MS): protocol for a randomised controlled trial

**DOI:** 10.1186/s13063-019-3768-7

**Published:** 2019-12-02

**Keywords:** Multiple sclerosis, Exercise, Physical activity, Individualised, Behaviour change strategy, Neurophysiotherapist, Randomised controlled trial

## Abstract

**Background:**

Multiple sclerosis (MS) is a chronic, degenerative disease of the central nervous system. Because of the long-term and unpredictable nature of the disease, the burden of MS is significant from both a patient and societal perspective. Despite a recent influx of disease-modifying therapies to treat MS, many individuals continue to experience disability that negatively affects productivity and quality of life. Previous research indicates that physical activity has a positive impact on walking function in individuals with MS, in addition to the usual beneficial effects on overall health. However, most people with MS are not active enough to gain these benefits, and a lack of support to initiate and maintain physical activity has been identified as a major barrier. This study will evaluate the impact of a novel intervention involving individualised behaviour change strategies delivered by neurophysiotherapists on increasing physical activity levels in individuals with MS who are currently inactive.

**Methods/design:**

This single-blind, parallel-group, randomised controlled trial will be conducted in Saskatchewan, Canada. Eligible participants include individuals with MS who are ambulatory but identified as currently inactive by the self-reported Godin Leisure-Time Exercise Questionnaire (GLTEQ). The intervention will be delivered by neurophysiotherapists and includes individualised behaviour change strategies aimed at increasing physical activity over a 12-month period. The control group will receive usual care during the 12-month study period. The primary outcome is the change in physical activity level, as measured by the change in the GLTEQ score from baseline to 12 months. Secondary outcomes include the change in patient-reported outcome measures assessing MS-specific symptoms, confidence and quality of life.

**Discussion:**

Physical activity has been identified as a top research priority by the MS community. Findings from this novel study may result in new knowledge that could significantly impact the management and overall health of individuals with MS.

**Trial registration:**

ClinicalTrials.gov, NCT04027114. Registered on 10 July 2019.

## Introduction

Multiple sclerosis (MS) is a chronic degenerative neurological disease involving the central nervous system. Symptoms of MS are unpredictable and can affect multiple body systems. The disease may be broadly categorised as relapsing-remitting or progressive [1]. Over time, most cases follow a progressive course [2], and an estimated 50% of individuals with MS require a cane within 15 years of disease onset [3]. There is no cure for MS, and although several different disease-modifying therapies are available, there is still controversy about their long-term effectiveness, and they are not indicated for all individuals with MS [4].

In the general population, people who are moderately physically active have a lower risk for medical co-morbidities and an increase in lifespan by an average of 7 years [5]. Physical activity has been shown to have considerable benefit in MS, regardless of disease type or duration [6]. Physical activity has also been proposed to have a disease-modifying impact [7], supported by magnetic resonance imaging outcomes [8] and research in animal models [9]. Regardless of evidence supporting a positive effect, less than 20% of individuals with MS are sufficiently active for health benefits [10]. Despite the known benefits of exercise in MS, there has been little change reported in physical activity levels in the MS population over the past 25 years [11]. Historically, the standard approach for promoting physical activity in MS research has involved structured exercise training [12]. However, individuals with MS routinely cite a lack of support and resources as a major barrier to regular physical activity [5]. A recent review on exercise interventions in MS identified the largest effect sizes for increasing physical activity were from those involving behaviour change strategies [13]. The same review noted that existing behaviour change strategy research was difficult to replicate and implement in clinical practice due to insufficient detail about the actual interventions [13].

In order to better describe the active components of behaviour change interventions and adopt the most effective behaviour change strategies, the Behavior Change Technique Taxonomy (BCTT) was created [14]. The BCTT includes a comprehensive list and definitions of behaviour change strategies. Behavior Change Theory describes the ‘why’ and informs selection of behaviour change strategies, or the ‘how’ [15, 16]. Few studies have applied theories of behaviour change in MS physical activity interventions [17], and those that have were focused largely on ‘packaged’ rather than individualised behaviour change interventions [18]. For example, fatigue in MS is identified as a major barrier to exercise [19]. A study may deliver a behaviour change intervention through a well-designed fatigue self-management programme; however, not every individual with MS will have fatigue as their main barrier to physical activity. Therefore, individualised behaviour change strategies that address each person’s unique and most significant barriers are recommended; yet, few have been applied in MS physical activity research to date [20].

Although effective at increasing physical activity behaviour, behaviour change strategies alone are believed to account for only 20% of change [16]. A recent study on behaviour change interventions recommended the added value of professional support [21], because individuals with MS benefit from the intermittent support of a specialist with expertise in exercise and MS to help maintain activity levels and function as the disease progresses [22]. The purpose of this study is to evaluate if a novel intervention of individualised behaviour change strategies delivered by neurophysiotherapists with expertise in MS increases physical activity levels in individuals with MS who are currently inactive.

## Methods/design

### Study design and setting

The IPAC-MS (Individualized Physiotherapy and Activity Coaching for Multiple Sclerosis) study is a prospective, single-blind, parallel-group, randomised controlled trial conducted in the Canadian province of Saskatchewan. The study is designed as a superiority trial and is a collaborative effort of interdisciplinary researchers, clinicians, and patient and family advisors Additional file 1.

### Study participants

Participants will be recruited primarily through the Saskatchewan MS Drugs Program (SMSDP). The SMSDP is a provincial initiative created to oversee the applications of all individuals applying for government coverage of a disease-modifying therapy for MS. At the time of enrolment in the SMSDP, individuals are offered the chance to consent to be contacted about participating in future MS-related research; those who consent are also asked to complete the Godin Leisure-Time Exercise Questionnaire (GLTEQ) [23–25]. Approximately 50% of all applicants to the SMSDP have consented and completed the GLTEQ. Individuals with a GLTEQ score < 24 are considered not sufficiently active for substantial health benefits and will be the primary cohort targeted for recruitment. If necessary, recruitment may also occur through the Saskatoon MS Clinic, the primary referral site for all Saskatchewan patients with MS, and through local MS Society organisations.

Individuals older than 18 years of age, with clinically definite MS, having a Patient Determined Disease Steps score ≤ 6 (i.e., able to walk with or without aids) [26], and who are estimated not to be sufficiently active for substantial health benefits (i.e., self-reported exercise less than four times weekly) are eligible for this study. Those who are unable to provide consent or are deemed to have a moderate-high risk for exercise-related harm based on the Physical Activity Readiness Questionnaire [27] will be excluded.

### Randomisation and blinding

All consenting participants who have completed a baseline assessment will be stratified into one of three categories based on their baseline GLTEQ score (< 9, 9–17, ≥ 18). Participants from each of the three strata will be randomly assigned to either the intervention or control group by a centralised telephone request to a study coordinator not involved in data collection or analyses. Randomisation lists were computer-generated in blocks of 4 to help achieve balance in the groups. The randomisation list was created prior to participant recruitment by a research team member not involved in data collection or analyses. Given the nature of the intervention, only the outcome assessors involved in the data collection will be blinded to the study group.

### Intervention and control

The intervention is an individualised physical activity behaviour change programme. The intervention will be delivered by neurophysiotherapists with expertise in MS over a 12-month period. Because each programme is specifically created for each individual, components of the intervention may vary between participants. However, there are three consistent features: behaviour change strategies, recommendations for physical activity, and ongoing neurophysiotherapist support. After randomisation, participants in the intervention group will undergo a tailored intake by a neurophysiotherapist, which will serve as the foundation for the individualised approach. At the initial intake, neurophysiotherapists will evaluate the participants’ individual attributes and physical activity needs in addition to a general physiotherapy assessment (e.g., MS symptoms and functional levels) to create personalised programmes. This initial intake may occur over one to three sessions and in variable formats, depending on the participants’ needs. To promote consistency, neurophysiotherapists will be trained in the Behaviour Change Wheel [28], the BCTT [14], and the Social Cognitive Theory of Behaviour Change, including correlates and determinants of physical activity behaviour in MS [20]. All training of the neurophysiotherapists was done with a standardised programme and delivered by the same instructor.

All physical activity recommendations made by the neurophysiotherapists will be based on established guidelines, existing resources, and individual participant needs. Best practice guidelines recommend that individuals with MS who have mild to moderate disability work up to at least 30 minutes of moderate intensity aerobic activity twice per week and resistance exercises for major muscle groups twice per week [29]. Support from a neurophysiotherapist will be available to the intervention group throughout the study period. We have allotted 15 neurophysiotherapist contact hours per participant, and each encounter will be recorded (method of contact, service delivered, and time required) using standardised data collection forms. The neurophysiotherapist support may occur in person, via telephone, using web-based methods and/or by telehealth. The neurophysiotherapist will record the types of behaviour change strategies used with each participant according to the framework and descriptors from the BCTT [14]. Intervention participants will also receive printed educational material from the MS Society of Canada on physical activity [29], diet [30] and stress management [31] at 2, 4 and 8 months. Because participants are involved in developing their own treatment plans, good adherence to the intervention is expected.

The control group will receive the same printed educational material as the intervention group at 2, 4 and 8 months. Participants in the control group will not receive any individualised assessments or recommendations, nor will they have access to neurophysiotherapist support throughout the 12-month study period (Fig. 1). At the end of the study, the control group participants will have the opportunity to receive the intervention; however, any results generated will not be part of the primary study analyses.

**Fig. 1 Fig1:**
[figure not shown]
Schedule of study enrolment, interventions, and assessments

### Study outcomes

The primary outcome is the change in physical activity level, as measured by the change in the GLTEQ score from baseline to 12 months. The GLTEQ is a validated self-reported measure of physical activity with sensitivity to detect change in MS exercise interventions [23, 24]. The GLTEQ requests activity levels in the week prior (minimising recall bias), is easy to administer, demonstrates good test-retest reliability in ambulatory individuals with MS, and correlates with other more costly and/or less convenient measures of physical activity in MS, such as accelerometers [32]. The total GLTEQ score is calculated according to the number of self-reported strenuous, moderate- or mild-intensity physical activity in 15-minute time blocks over the week. A total leisure activity score is then computed, which includes a correction for the estimated metabolic demands associated with these intensity levels. The total GLTEQ score (range, 0–119) is recommended for use in physical activity research in MS [25], with higher scores indicating greater activity levels. A score > 23 is considered sufficiently active for substantial health benefits [23, 25].

Secondary outcomes include the change in patient-reported outcome measures assessing MS-specific symptoms, confidence and quality of life. The Multiple Sclerosis Impact Scale v2 [33] is a self-administered questionnaire evaluating patient-perceived physical and psychological impact of their MS. The Multiple Sclerosis Self-Efficacy Scale is an MS-specific, self-reported, self-efficacy measure with strong psychometric properties [34]. The 18-item version will be used whereby participants rate their level of confidence regarding components of disease management using a 10-point scale (very uncertain to very certain). Self-efficacy has been identified as one of the most consistent correlates of physical activity [35]. The Exercise Self-Efficacy Scale [36] is a validated and reliable measure for MS. It is a patient-reported ordinal six-item measure whereby items are rated on a scale of 0 (not at all confident) to 100 (highly confident) and averaged to obtain a total score. All study outcomes will be measured at baseline and at months 3, 6, 9 and 12 in both study groups (Fig. 1). To avoid anticipation of surveys potentially influencing responses, participants will only be informed that they will receive survey requests at random times over the study period.

### Analyses

Baseline data collection will include both demographic and MS-related information (Table 1); the same information will be collected at the end of the 12-month study period for all participants. All analyses will follow the intention-to-treat principle. The primary outcome will be analysed with repeated measures analysis of variance (ANOVA) and mixed effects models to compare GLTEQ scores between the intervention and control groups at 12 months. A mixed effects model will incorporate missing data under the assumption of missing at random. Although the GLTEQ is an ordinal scale, we will treat it as continuous because this is common practice for this measure [37] and will allow comparisons with the existing literature. Further within-subject effect comparison at 12 months will be done using ANOVA. The group-by-time interaction will be explored using a mixed effects model after controlling for potential covariates. Similar analyses will occur for the secondary outcomes.

**Table 1 Tab1:** Baseline data collection variables

Variable	
Age (years)	
Sex	
Male	
Female	
Height	
Weight	
BMI	
Within normal limits	
Under normal limits	
Over normal limits	
Medical history	
Osteoarthritis	
Osteoporosis	
Coronary heart disease	
Stroke	
Diabetes	
Chronic respiratory disease	
Parkinson disease	
Cancer	
Other (list)	
Residence	
Urban	
Rural	
Type of MS	
Relapsing-remitting	
Secondary progressive	
Primary progressive	
Progressive relapsing	
Unknown	
Year of MS onset (e.g., first symptom)	
Year of MS diagnosis (by a neurologist)	
Most recent relapse (month/year)	
Walking aid or assistive device required?	
No	
Yes (if yes, list type)	
Employment	
Full-time (≥36 hours weekly)	
Part-time	
Casual	
Unemployed due to MS	
Retired	
Any falls in past 6 months?	
No	
Yes (frequency and severity)	
Disease-modifying therapy use	
Never	
Past (list)	
Current (list)	
Hospital Anxiety and Depression Scale (HADS) score	
Timed 25-ft walk (seconds)	
Nine-hole peg test (seconds)	
Symbol Digit Modality Test score	
Godin Leisure-Time Exercise Questionnaire score	
Multiple Sclerosis Impact Scale-29 v2 score	
Multiple Sclerosis Self-Efficacy Scale score	
Exercise Self-Efficacy Scale score	

*BMI* body mass index, *MS* multiple sclerosis

Using a conservative effect size of 0.3 for the primary outcome (change in GLTEQ), a power of 80%, and an alpha of 0.5, we estimate that 120 participants are needed for this study, allowing for 20% dropout. All statistical analyses will be conducted by the study biostatistician with use of SAS software (SAS Institute Inc., Cary, NC, USA), and all study data will be managed in REDCap (Vanderbilt, v6.7).

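### The 12-month GLTEQ contrast should come from a model with visit-specific variances: recruitment on low GLTEQ probably narrows the baseline spread, and a common-variance analysis would misstate the standard error

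*Protocol article*

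**What the plan says.** The Analyses section names the methods for the primary outcome: "The primary outcome will be analysed with repeated measures analysis of variance (ANOVA) and mixed effects models to compare GLTEQ scores" between the two arms at 12 months. It adds that the mixed model handles missing data under missing at random, and that a further within-subject comparison at 12 months will use ANOVA. It does not say how variances and correlations across visits are modelled, or whether baseline is one of the repeated responses or a covariate.

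Study outcomes defines the primary outcome as a change, "as measured by the change in the GLTEQ score from baseline to 12 months", and sets the visits: "All study outcomes will be measured at baseline and at months 3, 6, 9 and 12 in both study groups". On the scale it says "The total GLTEQ score (range, 0–119) is recommended for use in physical activity research in MS".

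GLTEQ also drives recruitment. Study participants says "Individuals with a GLTEQ score < 24 are considered not sufficiently active for substantial health benefits and will be the primary cohort targeted" for recruitment. The formal criterion is expressed as exercise frequency: "i.e., self-reported exercise less than four times weekly) are eligible for this study". Under Randomisation and blinding, participants are "stratified into one of three categories based on their baseline GLTEQ score (< 9, 9–17, ≥ 18", so the top stratum has no upper bound.

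**The concern.** GLTEQ is both the variable on which people are mainly recruited and the repeated outcome. Choosing people with low scores narrows the spread at baseline. Nothing holds scores down afterwards, and the intervention aims to raise them. Baseline variance is therefore likely to be smaller than the variance at months 3 to 12.

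The classical univariate repeated measures ANOVA, and a mixed model with only a random intercept and one residual variance, both assume the same variance at every visit and the same correlation between every pair of visits. If baseline is one of five levels in such a model, its small variance is averaged into the error used to judge month 12. The between-group comparison at 12 months is the trial's main answer, so its standard error, confidence interval and p-value would all be affected.

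**Working it through.** **Inputs**

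- Five visits (Study outcomes).
- 120 participants with 20% dropout (Analyses): 120 × 0.8 = 96, or 48 per arm if allocation is 1:1, which is assumed. The number per arm cancels from the ratios below and matters only for the simulation.
- Baseline SD: not given. Whole-number scores spread evenly over 0 to 23 have SD √((24² − 1)/12) = 6.92; a continuous spread gives 23/√12 = 6.64. I use 7. If scores stay within 0 to 23, the largest possible SD is 11.5 (half at 0, half at 23).
- Follow-up SD: not given. I assume 12 to 24, constant over months 3 to 12.
- Two-sided 5% test, assumed. The sample size paragraph prints alpha as 0.5, which is a separate matter.

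The article gives no SD or standard error by visit, so there is no figure of its own to reproduce.

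**Step 1: difference in level at 12 months.** A common-variance model uses the mean of the five visit variances where the month-12 variance is needed. With baseline SD s0 and follow-up SD sf:

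SE ratio (model/true) = √((s0² + 4·sf²)/(5·sf²)); type I error = 2·(1 − Φ(1.96 × ratio)).

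| sf (s0 = 7) | Calculation | SE ratio | Type I error |
|---|---|---|---|
| 12 | √(625/720) | 0.932 | 6.8% |
| 15 | √(949/1125) | 0.918 | 7.2% |
| 20 | √(1649/2000) | 0.908 | 7.5% |
| 24 | √(2353/2880) | 0.904 | 7.7% |

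As s0 becomes negligible the ratio tends to √0.8 = 0.894, a type I error of 8.0%. That is the ceiling for baseline narrowing alone. In the other direction, s0 = 11.5 with sf = 12 gives √(708.25/720) = 0.99 and 5.2%; s0 = 11.5 with sf = 24 gives √(2436.25/2880) = 0.92 and 7.1%. With equal SDs the ratio is 1.

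**Step 2: change from baseline to 12 months.** The common-variance model uses 2 × (mean variance − mean covariance). The true value is s0² + sf² − 2 × (covariance of baseline and month 12). Two examples with s0 = 7 and sf = 20, where the mean variance is 1649/5 = 329.8:

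- Correlation 0.7 among follow-up visits and 0.3 with baseline. Mean covariance = (4 × 42 + 6 × 280)/10 = 184.8. Model 2 × 145.0 = 290; true 49 + 400 − 84 = 365. Ratio √(290/365) = 0.89, type I error 8.1%.
- Correlation 0.3 among follow-up visits and 0.2 with baseline. Mean covariance = (4 × 28 + 6 × 120)/10 = 83.2. Model 2 × 246.6 = 493.2; true 49 + 400 − 56 = 393. Ratio √(493.2/393) = 1.12, type I error 2.8%.

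Over constant follow-up SDs of 12 to 25 and the correlations tried, the ratio ran from 0.80 to 1.13 and type I error from 2.7% to 11.6%. Unequal correlations contribute here as well: with SD 7 at every visit the change ratio was still 0.76 to 0.96.

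**Step 3: simulation under no effect** (20,000 trials per setting, 48 per arm, complete normal data, follow-up correlation 0.5 or 0.7, baseline correlation 0.3).

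| SDs (baseline; follow-up) | Pooled, level | Pooled, change | Own variance, level | Own variance, change |
|---|---|---|---|---|
| 7; 15 | 7.0%–7.3% | 4.4%–8.1% | 4.7%–5.1% | 4.9%–5.0% |
| 7; 20 | 7.7% | 4.7%–8.4% | 5.1%–5.3% | 5.1% |

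The formula is confirmed, and visit-specific variances restore about 5%.

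**Step 4: dependence on the follow-up trend.** If SD rose over months 3 to 12 as 12, 15, 18, 20, the level ratio would be √(228.4/400) = 0.76 (type I error 13.9%). If it fell as 20, 18, 15, 12, the ratio would be √(228.4/144) = 1.26 (1.4%). These results come mostly from the assumed trend: with the rising SDs, pooling the four follow-up visits without baseline still gave 10.3% to 10.6% in simulation.

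**The case against.** The strongest objection is that the article nowhere says one variance is pooled. A mixed effects model can carry an unstructured covariance, and a repeated measures ANOVA can use contrast-specific error terms or a sphericity correction. The remedy is thus compatible with the current text, and covariance structure is usually settled in a full protocol or SAP. All of this stands. A reader might infer that the plan commits the trial to an anticonservative primary test; the article does not support that. What survives is that repeated measures ANOVA is itself a named primary analysis, and its plain form is poorly suited to an outcome that is also the recruitment variable.

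A reader might also infer that baseline is confined to 0 to 23. It is not. GLTEQ below 24 is a recruitment target, applied to a score collected at enrolment in the provincial drug programme. The trial baseline is a separate assessment, the eligibility criterion contains no GLTEQ cut-off, and the top stratum is open. Likewise, 119 is the top of the scale and not an expected spread. Narrowing is likely, but its degree is unknown.

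Third, a standard error that is usually too small cannot be claimed for the stated outcome, change from baseline: Step 2 shows both directions. Nor can a type I error of about 14% be attributed to eligibility, since it needs a growth in SD for which the article gives no basis. The overall group-by-time F test is little affected (4.7% to 6.5% in simulation).

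Finally, participants are not selected on the secondary outcomes, so this argument does not carry over to them by itself.

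**Conclusion.** The point holds as a conditional one. If the 12-month contrast is taken from a common-variance analysis with baseline as one of five visits, its standard error will be wrong. For the difference in level it would be about 7% to 10% too small, with type I error of about 7% to 8%, assuming a baseline SD near 7 and a constant follow-up SD of 12 to 24. That excess shrinks towards zero as the baseline SD approaches the follow-up SD. For change from baseline the direction depends on correlations and on the trend in SD, which the article does not give. The size rests wholly on assumed values. The secure part is that a pooled error term is an unsafe basis for this contrast, and that a better one costs almost nothing. This is a worthwhile improvement to the Analyses section, not a demonstrated error in it.

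**What to change.** In the Analyses section, state that the single primary 12-month contrast comes from a likelihood-based repeated measures model with unstructured covariance (a separate variance for each visit and a separate covariance for each pair), with Kenward-Roger degrees of freedom. Baseline GLTEQ should either be a covariate or stay in the response vector with its mean constrained equal across arms. The second option keeps participants who have no follow-up in the model. In either form the group difference in the 12-month score equals the group difference in change, so the analysis matches the stated outcome. Name a heterogeneous-variance fallback in case of non-convergence: heterogeneous Toeplitz, then heterogeneous compound symmetry. State that the primary test will not be taken from a common-variance repeated measures ANOVA or a random-intercept-only model.

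The cost is a sentence or two of text and a change of option in the SAS code, with no new data or participants. The downside is more covariance parameters: 5 × 6/2 = 15 with baseline as a response, or 4 × 5/2 = 10 with it as a covariate, against 2 under the common-variance form. That brings a small convergence risk in roughly 100 to 120 participants and possibly a somewhat larger 12-month standard error.

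### The primary 12-month comparison names neither baseline GLTEQ nor the randomisation strata built from it; analysed as written, standard errors would be too wide and power lost

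*Protocol article*

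**What the plan says.** The protocol article, Randomisation and blinding, says that participants "will be stratified into one of three categories based on their baseline GLTEQ score (< 9, 9–17, ≥ 18"), with allocation in blocks of 4 within each band. Under Study outcomes, the primary outcome is change in GLTEQ from baseline to month 12, measured at baseline and at months 3, 6, 9 and 12.

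Under Analyses, the primary method is repeated measures ANOVA and "mixed effects models to compare GLTEQ scores between the intervention and control groups at 12 months". No fixed effects are listed for that comparison. Covariates come up once, in a later sentence: "The group-by-time interaction will be explored using a mixed effects model after controlling for potential covariates". They are not named there, although baseline GLTEQ is among the Table 1 variables.

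**The concern.** Baseline GLTEQ was judged important enough to stratify on, and it is likely to predict the 12-month score. Stratifying makes the arms more alike at baseline, so the estimated difference varies less from trial to trial. A model without the stratum or baseline does not know this. It leaves the baseline-related variance in the residual and reports a standard error that is too large.

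Naming a repeated measures method does not settle the matter. If each arm has its own baseline mean, the month-12 contrast is a raw difference and the group-by-time contrast is a change-score difference. Neither uses baseline efficiently. What is at stake is precision in a small trial, and whether baseline adjustment is fixed in advance or chosen later from an open list of covariates.

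**Working it through.** **Inputs from the article.** The plan states "Using a conservative effect size of 0.3 for the primary outcome (change in GLTEQ"), "a power of 80%, and an alpha of 0.5", and "we estimate that 120 participants are needed for this study, allowing for 20% dropout". Evaluable: 120 × 0.8 = 96, or 48 per arm, taking 1:1 allocation from two groups and blocks of 4.

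**The plan's own figure.** For a two-sample comparison, power = Φ(d√(n/2) − z) + Φ(−d√(n/2) − z). With d = 0.3 and n = 48, d√24 = 1.470. At a two-sided alpha of 0.5 as printed, z = 0.674, so power = Φ(0.796) + Φ(−2.144) ≈ 0.80, and 96/0.8 = 120. The stated figure is reproduced. At two-sided 0.05 the same 48 per arm gives Φ(1.470 − 1.960) ≈ 31%, and 80% power would need about 438 randomised. That is a separate problem; the checks below use 0.05.

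**Assumption.** The article gives no r, so 0.3, 0.5 and 0.7 are used.

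**Nominal variance of the 12-month contrast, 12-month SD = 1, equal SDs.** Raw: 1. Change score: 2(1 − r). Baseline-adjusted: 1 − r². Adjustment therefore cuts the nominal variance against raw by r² = 9%, 25% and 49%.

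**True behaviour under stratified randomisation.** Simulation with 96 participants, blocks of 4 in three baseline strata, normal data and 4,000 runs per r (Monte Carlo error about 0.3 points on a rate near 4.5%):

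| r | Raw: model SE | Raw: true SE | Raw: type I error | Adjusted: true SE | Adjusted: type I error |
|---|---|---|---|---|---|
| 0.3 | 0.204 | 0.198 | 4.5% | 0.196 | 5.5% |
| 0.5 | 0.204 | 0.184 | 3.1% | 0.177 | 4.9% |
| 0.7 | 0.204 | 0.160 | 1.3% | 0.144 | 5.2% |

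Repeat simulations, including a skewed baseline kept below 24, moved the raw type I error by a few tenths of a point; about 4.3% to 1.3% is a fair summary. The true variance cut is 1 − (0.196/0.198)² = 2% at r = 0.3, 1 − (0.177/0.184)² = 7% at 0.5 and 1 − (0.144/0.160)² = 19% at 0.7. With the skewed, restricted baseline, which is closer to this trial, the cut at 0.7 is about 15%.

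**Power at r = 0.6, d = 0.58** (roughly the difference detectable with 80% power at 48 per arm if stratification is ignored). With a normal baseline cut into thirds, the strata carry 0.793 of its variance: the outer thirds have means ±1.091, and (2/3) × 1.091² = 0.793. True SE of the raw contrast: √((1 − 0.36 × 0.793)/24) = 0.1725. Raw power: Φ((0.58 − 1.986 × 0.204)/0.1725) = Φ(1.01) ≈ 84%. Adjusted SE: √(0.64/24) = 0.163; power Φ(0.58/0.163 − 1.986) = Φ(1.57) ≈ 94%. Simulation gives 84–86% and 94%.

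**Power at the plan's d = 0.3.** At r = 0.5: 28% raw, 28% change score, 38% adjusted. At r = 0.7: 26%, 47% and 53%.

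**Against a change score.** With equal SDs the nominal variance ratio, adjusted to change, is (1 + r)/2, so the cut is 35%, 25% and 15% at r = 0.3, 0.5 and 0.7. The change contrast is also conservative (type I error about 2.0%, 3.0% and 3.7%), so the true cut is smaller: from the same simulation, true SEs of 0.206, 0.182 and 0.146 against 0.196, 0.177 and 0.144 give about 9%, 5% and 3%. If the month-12 SD is k times the baseline SD, the nominal ratio is k²(1 − r²)/(1 + k² − 2rk). At an assumed k = 1.5 this is 1.89/2.05 at r = 0.4 (an 8% cut) and 1.44/1.45 at r = 0.6 (under 1%).

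**The case against.** The strongest reply is that the article is silent and does not exclude adjustment. It names methods without listing terms; baseline enters through the change outcome and as the first repeated measure; and a full protocol or analysis plan, not shown, may fix the model. A mixed model with a common baseline mean across arms has exactly the baseline-adjusted variance, so the named method could already deliver the gain. This stands. A reader might infer that the trial does not adjust, but the text does not say so.

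It does not dispose of the point. The article does state the primary comparison, places covariates only in a separate exploratory model, and names repeated measures ANOVA, which ordinarily gives each arm its own baseline mean. Followed as written, the analysis is inferior to one the trial can have for nothing.

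A reader might also take the 9% to 49% nominal cut as the real gain in precision, or set 94% power against a nominal 80%. Neither is right: much of the variance has already been removed by the stratified design, so the raw analysis mainly misreports its precision. Finally, recruiting mainly people with GLTEQ below 24 may lower r, and at r = 0.3 the gain is small.

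**Conclusion.** The point holds in a limited form. The stated primary comparison omits the variable on which randomisation was stratified. If that omission is carried into the analysis, intervals are too wide and tests conservative: true type I error about 4.3% down to 1.3% for r from 0.3 to 0.7, with a real loss of power (about 84–86% against 94% at r = 0.6 and d = 0.58). There is no bias and no excess of false positives. The sizes rest on an assumed r, 48 evaluable per arm and two-sided 0.05. The advantage over a change-score analysis is smaller, and near zero if the month-12 SD is well above the baseline SD and r is around 0.6 to 0.7.

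It should not be read as a rescue of the sample size. For d = 0.3 with 80% power, adjustment brings the number to randomise from 438 to 398, 328 or 223 at r = 0.3, 0.5 or 0.7; 96 evaluable would be enough only at r of about 0.85.

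**What to change.** State the primary model before the analysis: a mixed model for GLTEQ at months 3, 6, 9 and 12 with arm by visit, continuous baseline GLTEQ with its visit interaction, and the three-level randomisation stratum as fixed terms. A constrained model with baseline among the responses, a common baseline mean across arms and the stratum as a fixed term serves the same aim. Report the adjusted arm difference at month 12 as the primary estimate. Once baseline is a covariate, the adjusted difference in score equals the adjusted difference in change, so this also fits the outcome as defined under Study outcomes. Adjust each secondary outcome for its own baseline in the same way.

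The cost is a line or two of model specification and a few degrees of freedom. Every variable is already collected, and no participants or visits are added. The sample-size statement needs separate correction.
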